**Hypotheses**

The hypothesis to be tested is that biomarkers of neurotrauma may give specific prognostic information for an individual patient to inform acute and sub-acute treatment stratification and future prognosis. Measurements of biomarkers taken after trauma will be correlated with outcome measures at 6 and 12 months.

Secondary hypotheses are that novel biomarkers exist and may be identified; genetic factors are important modulators of outcome.

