**Study Design**

This is a cohort study to categorise the traumatic brain injury population at UHB. Brain biomarkers, serum, micro-diasylate, CSF and imaging will be measured in two groups of patients. Outcome will be assessed by TMS threshold, ERP, ERG, VEP and cognitive and psychological questionnaires will be performed. The two groups of patients will be:

The study group - patients who have suffered a head injury presenting or transferred to UHB.

The control group - patients admitted with non-head trauma matched to the study group by ISS severity and demographic.

Patients for inclusion will be identified at point of injury or as soon as possible after presentation to UHB upto 1 hour post injury. For samples taken pre-hospital where patients are unable to consent these will be taken, subject to a favourable REC opinion under the Mental Capacity Act ‘waiver’ for research in emergency situations. Advice will be sought from a consultee as soon as practicable following presentation to hospital and consent will be sought from the patient once capacity has been regained. Information in the form of the included Patient Information Sheets or Consultee Information Sheet will be provided; consent or advice will be recorded on the appropriate written forms annexes c-i.

*Inclusion criteria:*

Study group - Patients who have sustained a head injury resulting in presentation to UHB within 1 hour of injury.

Control group - non-head trauma patients matched to control by severity (ISS) and demographic.

*Exclusion criteria:*

Children under the age of 18 years. For the control group those with a recent head injury or known neurological condition.

Our conservative assumption is that 80% of head injured patients will show a positive biomarker response with 10% of non-head injured patients showing a positive response. Using fishers Exact test (power0.9; alpha 0.05; 1:1 control subject ratio) would predict 10 patients in each group. However head injuries and trauma in general demonstrates much heterogeneity and to allow comparison across modalities and sub-groups we intend to recruit up-to 100 patients to the study group and the control group.

*Sampling - Blood*

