Sampling of blood will be performed at regular intervals beginning at point of injury through to follow-up at six months post injury. During emergency treatment at point of injury venous access is gained to allow the delivery of drugs and fluids. Blood samples are not usually withdrawn as there are no current clinical investigations available at that time-point. We propose to withdraw 20mls of venous blood for early biomarker analysis. Blood samples are taken routinely over the following days of admission to monitor various factors, where feasible research samples will be withdrawn alongside clinical samples.

Blood samples will be analysed for an array of biomarkers with particular interest in early markers with short half-lives. Specifically S100B, Glial fibrillary acidic protein, myelin basic protein, micro-particle analysis and metabolomics assays will be performed. Genetic analysis will be performed initially looking at susceptibility or protective factors with differing mtDNA haplotypes.

*Micro-dialysis*

Intra-cranial pressure monitoring and more lately micro-dialysis catheter monitoring are part of routine clinical care for head trauma allowing monitoring of intra-cranial pressure and brain oxygen tension; important clinical variables. Micro-dialysis is a technique that involves the placement of a catheter containing a semi-permeable membrane into a tissue. A fluid is then circulated over this membrane and small-molecule substances in the tissue will then diffuse across the membrane allowing analysis to be performed to detect those of interest, this fluid is known as a diasylate. Although this technique was first developed 50 years ago it has only recently been adopted into routine clinical practice in certain centers. Presently the diasylate is discarded following bedside measurement of oxygen, however this fluid could provide a wealth of potential biomarkers, we propose to recover the fluid for analysis. Control patients would not be expected to have ICP monitors of micro-dialysis catheters as these are solely used in the setting of neurosurgical problems.

*CSF*

CSF (cerebrospinal fluid) samples may be withdrawn as part of routine clinical management, particularly where extra-ventricular drains or similar have been placed. Where this happens we propose to withdraw an additional sample of CSF for analysis.

*Imaging*

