**Methodology**

1. Patient Recruitment: All trauma patients with a survivable injury and ISS (decision) will be entered into the study. 100 trauma patients with a brain injury and 100 trauma patients without a brain injury will be studied. The study team will liaise with the emergency department at UHB for local trauma.
   1. Patient journey: Demographics will be entered into a patient database, a schedule of sampling will then be generated to allow the patient to be followed through the study.
   2. Insults: initial injury and insults - baseline GCS score, post-traumatic amnesia, surgical intervention, infection, sepsis, ICP, cerebral blood flow and oxygenation, seizure.
   3. Timings: Admission, surgery, ventilation days, ICU days, discharge, rehabilitation, time to recovery.
2. Measurements and sample collection: The following measurements will be made on samples taken from point of injury through to six month follow-up. The schedule appears in table 1.
   - 1. *Venous blood*. Venous access for drugs and fluids is gained early in trauma care at point of injury, however blood would not routinely be withdrawn as there are no useful clinical tests at this stage currently. We propose to withdraw 20mls at this point for analysis of the early biomarker milieu. An additional 20mls of venous blood will be taken at subsequent time-points. These will be analysed for biomarker levels and metabolomics. Genomic analyses will be carried out on mitochondrial and nuclear DNA, including mitochondrial DNA haplogroups, Apoliprotein E haplotypes and genes of the MToR pathway.
   1. *Micro-diasylate*. Micro-dialysis is used in routine clinical practice to monitor cerebral perfusion. The small amount of diasylate generated would normally be discarded in clinical practice, we propose to recover it for analysis. The diasylate will be snap frozen following recovery and sent to DSTL for analysis.
   2. *CSF*. Where CSF is withdrawn in normal clinical practice an additional 5 mls will be withdrawn for biomarker analysis.
   3. *Imaging.* MRI, MRS, DTI, will be performed in accordance with the schedule at table 2.
      1. MRI: T1, T2, FLAIR, DWI, ADC sequences will be acquired on a 1.5T scanner in the UHB inpatient imaging department.
      2. MRS: sequences will be acquired on a 1.5T scanner in the UHB inpatient imaging department.
      3. DTI: sequences will be acquired on a 1.5T scanner in the UHB inpatient imaging department.

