**Statistical Analysis**

Data will be analysed using SPSS. Descriptive statistics will be determined on parametric and non-parametric data. The independent variables are age, sex, ISS/NISS, type of injury, MTOR activity status. The primary dependent variables include biomarker levels, imaging analysis, TMS threshold and cognitive/psychological scoring. Exploratory assessment of data will be completed using analysis of co-variance and ordinal analysis of outcome. The spread of the means will be given as standard error of the mean. Differences in the means are considered significant if p<0.05. Psychological and cognitive scoring will undergo correlation analysis using Spearman’s rank correlation coefficient. They will also be subject to Rasch analysis. Multivariate regression analysis will be used to identify factors with significant impact on outcome.

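### Identifying prognostic factors by significance in at most 100 head-injured patients is likely to exaggerate the markers selected and to lose real clinical predictors

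*Protocol*

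**What the plan says.** - **Use of the regression** (Statistical Analysis): "Multivariate regression analysis will be used to identify factors with significant impact on outcome". Covariance and ordinal analyses are labelled exploratory in that section; this sentence is not.
- **Threshold** (Statistical Analysis): "Differences in the means are considered significant if p<0.05". This is worded for means. Applying it to regression factors is an inference, though a natural one.
- **Variable roles** (Statistical Analysis): "The independent variables are age, sex, ISS/NISS, type of injury, MTOR activity status", followed by "The primary dependent variables include biomarker levels, imaging analysis, TMS threshold and cognitive/psychological scoring". No biomarker level is among the independent variables.
- **Purpose** (Hypotheses): "biomarkers of neurotrauma may give specific prognostic information for an individual patient", with marker measurements to be correlated with outcome at 6 and 12 months.
- **Sample**: Methodology says "100 trauma patients with a brain injury and 100 trauma patients without a brain injury will be studied"; Study Design makes this a ceiling: "we intend to recruit up-to 100 patients to the study group and the control group".
- **Candidate markers** (Study Design, blood sampling): "Specifically S100B, Glial fibrillary acidic protein, myelin basic protein, micro-particle analysis and metabolomics assays will be performed". Mitochondrial and nuclear genetic markers, imaging findings, microdialysate and CSF come on top.
- **Primary outcome** (Outcome Measures): Glasgow Outcome Score (GOS) at 6 months. No expected distribution is given.

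**The concern.** Finding factors by significance is a poor route to individual prognosis when candidates are many and patients few. A coefficient that passes a p-value threshold in a small sample tends to be one that chance has enlarged, so even a correctly flagged marker looks stronger than it is. A true predictor with a moderate effect often misses the threshold and is lost. A model built this way predicts less well in new patients than it appears to in the patients who produced it.

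This is partly distinct from multiplicity. Controlling the number of false positives would not remove the inflation in the true positives.

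At stake is the main hypothesis. A marker intended to inform treatment stratification could be carried forward with an exaggerated effect, and without a fair comparison against what age and injury severity already tell the clinician.

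**Working it through.** **1. The protocol's own calculation.** Study Design assumes 80% versus 10% positive response, Fisher's exact test, power 0.9, alpha 0.05 and a 1:1 ratio, and gives 10 per group. Exact enumeration gives power 0.937 one-sided and 0.841 two-sided at n = 10; two-sided power reaches 0.905 at n = 11. The figure is therefore reproduced exactly one-sided and within one patient two-sided, which is immaterial with up to 100 per group planned. It sizes a two-group comparison of positive response. It does not support a prognostic model, and no calculation accompanies the increase to 100.

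**2. Candidate count.** Table 1 has three early blood draws: point of injury (the emergency department draw only replaces a missed one), 6-12 hours, and day 3.
- 3 proteins × 3 draws = 9
- 9 + 5 listed independent variables = 14

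This is before micro-particles, metabolomics, genes and imaging.

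**3. Events per candidate.** The protocol gives no GOS distribution. Assume a binary GOS with 20-40% unfavourable among 100 head-injured patients:
- 20 / 14 = 1.4
- 30 / 14 = 2.1
- 40 / 14 = 2.9

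**4. Simulation with backward elimination at p<0.05.** Assumptions: 100 patients, age and ISS each with a log odds ratio of 0.5 per SD, all other markers null. AUC is compared in the same patients and in new patients.

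| Model (20-40% events, 9-15 null markers) | Apparent AUC | New-patient AUC |
|---|---|---|
| Backward elimination | 0.68-0.71 | 0.59-0.62 |
| Full model, no selection | 0.76-0.84 | 0.59-0.62 |
| Age and ISS always kept, no markers | – | about 0.67 |

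The gap after backward elimination is about 0.08-0.12. When one marker is made truly prognostic, its coefficient, if selected, is inflated about 1.7 times.

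**5. What the markers add, and what they do not.** Same set-up at 30% events, 300 simulated studies per setting:

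| Null markers | Apparent AUC | New-patient AUC | Gap | Each clinical predictor dropped |
|---|---|---|---|---|
| 0 | 0.65 | 0.61 | 0.04 | 48% |
| 9 | 0.69 | 0.615 | 0.075 | 41% |
| 15 | 0.70 | 0.60 | 0.10 | 46% |

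The shortfall from about 0.67 to about 0.61 is already there with no markers. It comes from low power to retain age and ISS. The markers raise the apparent AUC.

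**6. A different selection rule.** Fit all candidates, keep those with p<0.05, refit. Assumptions: 80-100 patients, 30-40% events, two true predictors with log odds ratio 0.5 per SD. AUC is averaged over the simulated studies that retained a factor.

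| Total candidates | Apparent minus new-patient AUC | Inflation of selected true predictors |
|---|---|---|
| 5 | 0.06-0.08 | 1.4-1.7 times |
| 10 | 0.08-0.11 | 1.6-1.8 times |
| 15 | 0.10-0.13 | 1.7-2.2 times |
| 20 | 0.12-0.15 | 1.8-2.5 times |

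Even if only the five listed independent variables entered, the optimism would not vanish.

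**The case against.** The strongest case against is that most of this analysis is not in the protocol.

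- **No accuracy measure or same-data evaluation is stated.** A reader might infer that the model will be judged on the patients who produced it and that its accuracy will therefore be overstated. The protocol names no AUC, calibration or risk score, and an analysis plan not shown here may add validation or shrinkage. This stands: only a conditional statement is supported.
- **Backward elimination is not prescribed.** Also true. The sentence is compatible with one full model and significance tests on its terms. That does not rescue it: any accuracy read from such a model on the same patients is more optimistic still (0.76-0.84 against 0.59-0.62), and looking only at the significant terms still exaggerates them.
- **Biomarkers are listed as dependent variables.** True, and the 14 candidates are assembled from several sections. But the hypothesis cannot be tested without markers on the predictor side, and Outcome Measures says markers will be related to outcome. The roles conflict and need reconciling.
- **The binary GOS, the event rate and the exclusion of controls are assumptions.** True. The protocol mentions an ordinal analysis, which would use more information, and does not say whether controls enter the regression.
- **Markers displacing clinical predictors.** A reader might infer that uninformative markers push age or ISS out of the model. The second table does not show this: those predictors are dropped about as often with no markers.
- **Overlap with multiplicity.** The chance of retaining at least one null marker is close to 1 − 0.95^9 = 0.37 for 9 markers and 1 − 0.95^15 = 0.54 for 15. That part is family-wise error and is not counted here. The inflation of true effects is separate.
- **The stated aim is to characterise relationships.** This softens the consequence, but the hypothesis itself speaks of individual prognosis and treatment stratification.

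**Conclusion.** The concern holds in a conditional form. The protocol makes significance the means of identifying factors, for a prognostic hypothesis, with many candidate markers and at most 100 head-injured patients. That choice is likely to exaggerate the effects of selected markers, and any accuracy read from the same patients unless it is corrected. It also often drops real clinical predictors, through low power.

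Under the assumptions of step 4, the AUC optimism is about 0.08-0.12 after backward elimination, and a selected true marker is inflated about 1.7 times. A model that keeps age and ISS reaches about 0.67 in new patients, against about 0.60 for the selected model. These sizes move with the number of candidates, the outcome distribution and any correction applied, none of which the protocol gives. The documents do not show that reported accuracy will be overstated. What they fix is a rule that makes it likely unless something is done. The sentence should be changed, but the point does not threaten the study's data collection.

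**What to change.** Replace the regression sentence in Statistical Analysis with a commitment along these lines:

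1. The baseline clinical variables (age, sex, ISS/NISS, type of injury) stay in the outcome model whatever their p-values.
2. Biomarkers enter that model as predictors, with penalised estimation for any wider marker set. The list of independent and dependent variables is amended so that it agrees with Hypotheses.
3. The result reported is the gain over the clinical model, with bootstrap optimism correction that repeats every selection step.

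Naming in advance one marker at one early draw for the main claim would sharpen the test further, but is optional.

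The cost is some extra analysis work and possibly software beyond SPSS. No further patients or samples are needed. Reported accuracy will look less favourable.

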**Outcome Measures**

Outcome of brain trauma will be assessed with cognitive and psychological symptom scoring, TMS threshold measurement and ERP. Initial severity scoring will be assessed with ISS/NISS. Changes in biomarkers will be measured in relation to brain trauma versus non-brain trauma and related to the above outcome assessment.

The primary outcome will be functional status as measured by the Glasgow Outcome Score at 6 months. Secondary outcome measures are functional status as assessed by the Glasgow Outcome Score at 12 months; cognitive and psychological symptom scoring with Post­concussion Symptom Questionnaire­19 (PCSQ­19), Impact of Events Scale – revised (IES­r), Depression and Anxiety Symptom Scale – 21 (DASS­21), PTSD checklist (PCL), Patient Health Questionnaire (PHQ), neurological assessment battery NAB-SM.

Other seconday outcome measures are neurophysiology measures of TMS threshold and Event related potentials.

Developing a better understanding of the relationships surrounding severe brain trauma and biomarkers in development will lead to better clinical understanding, categorisation, prognostication and treatments, both in targeting existing interventions and through development of new treatment in future interventional studies.

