**Background**

Through the collaboration of the UHB, DSTL and University of Birmingham we wish to characterise the biomarker response to traumatic brain injury and define the roles of biomarkers relating to injury detection, diagnosis, monitoring, classification, prognosis and treatment. This will form a basis for future interventional studies to improve outcome from traumatic brain injury.

This study draws from two previous studies, Biomarkers of Brain Injury and Steroids and Immunity from Injury through to Rehabilitation study. The former aimed to identify novel biomarkers in a severe brain trauma population; the latter included a sub-population of severe brain trauma and looked at a small range of biomarkers. The major weaknesses in both of these studies were a limited appraisal of outcome following brain trauma as opposed to severity at inclusion and limited follow-up of participants. We aim to build on these studies with a broader population and comprehensive assessment of outcome.

Studies carried out have not fully defined the role of biomarkers in clinical practice; few have made a transition to routine practice.

*Traumatic Brain Injury (TBI)*

There is increasing interest in TBI and it remains a leading cause of morbidity and mortality in particular affecting the young with a male preponderance. Although previously reported to be an untreatable cause of mortality there have been improvements, particularly when treatment is given in specialist neurosurgical centers irrespective of need for surgical intervention as recommended by NICE in the UK. At present treatment is largely supportive and investigational techniques have not changed apace clinically with the research field.

*Biomarkers in Brain Injury*

A biomarker in the broadest sense is any characteristic that may be objectively assessed to provide an indicator of a normal or abnormal disease or physiological state of an organism, this includes imaging and laboratory tests along with more simple clinical findings. Biomarkers are used in other clinical settings such as Troponin for cardiac damage.

There has been much interest in the development of biomarkers for neuro-trauma though this has yet to lead to a change in clinical practice. Previous research has assessed potential biomarkers, for instance Creatine kinase, glial fibrillary acidic protein, myelin basic protein and S100B. S100B has been the most intensely studied and has since been shown not to be specific to CNS damage.

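### With no head-injury severity floor in force, the five-level Glasgow Outcome Score risks a ceiling effect on the primary outcome; the extended scale would reduce it at little cost

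*Protocol*

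**What the plan says.** Outcome Measures fixes the primary endpoint: "The primary outcome will be functional status as measured by the Glasgow Outcome Score at 6 months". It then repeats the instrument: "Secondary outcome measures are functional status as assessed by the Glasgow Outcome Score at 12 months". The extended version is not named anywhere in the protocol.

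Three places bear on who is scored:

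- Study Design, inclusion criteria, study group: "Patients who have sustained a head injury resulting in presentation to UHB within 1 hour of injury". No GCS, ISS or other severity limit is attached.
- Methodology, patient recruitment: "All trauma patients with a survivable injury and ISS (decision) will be entered into the study". No ISS value follows. Survivability trims only the worst end.
- Background, on earlier work in severe brain trauma: "We aim to build on these studies with a broader population and comprehensive assessment of outcome".

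On use of the outcome, Hypotheses says: "Measurements of biomarkers taken after trauma will be correlated with outcome measures at 6 and 12 months". Statistical Analysis says: "Exploratory assessment of data will be completed using analysis of co-variance and ordinal analysis of outcome".

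Outcome Measures also names finer secondary measures: PCSQ-19, IES-r, DASS-21, PCL, PHQ, NAB-SM, TMS threshold and event-related potentials. Table 3 schedules questionnaires at days 180 and 360 and TMS and ERP at day 360. It does not list the Glasgow score.

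**The concern.** The standard Glasgow Outcome Score has five levels: death, vegetative state, severe disability, moderate disability and good recovery. The extended version splits each of the last three in two, giving eight. The protocol does not state these levels; they are taken here as the standard structure of the instruments.

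On the five-level score, every patient in good recovery gets the same value, whether recovery is full or incomplete. A biomarker that distinguishes those two groups cannot show it on the primary endpoint, and the tie costs precision in any rank or ordinal analysis. The cost rises steeply with the share of patients in the top category. With no severity floor in force, nothing in the eligibility text keeps that share low. This sits awkwardly with a study whose stated purpose is individual prognosis and whose rationale is that earlier studies appraised outcome too narrowly.

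**Working it through.** **The plan's own figure.** The only sample-size calculation (Study Design) compares 80% with 10% biomarker positivity by Fisher's exact test, power 0.90, alpha 0.05, and gives 10 per group. Exact enumeration gives one-sided power of 88.8% at 9 and 93.7% at 10 per group, so 10 is reproduced one-sided. Two-sided, power is 84.1% at 10 and 90.5% at 11. This calculation does not use the Glasgow score, so it neither supports nor contradicts the point. The plan offers no outcome distribution to work from, so only a range can be given.

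**Information index.** In a proportional-odds analysis, information is proportional to 1 − Σp³, where the p are the category proportions. All distributions below are assumptions. Each eight-level set collapses exactly to its five-level set.

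| Good recovery | Five levels (death to good recovery) | Eight levels |
|---|---|---|
| 25% | .30, .03, .20, .22, .25 | .30, .03, .12, .08, .11, .11, .12, .13 |
| 50% | .12, .02, .14, .22, .50 | .12, .02, .08, .06, .10, .12, .22, .28 |
| 70% | .05, .01, .09, .15, .70 | .05, .01, .05, .04, .06, .09, .30, .40 |

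| Good recovery | 1 − Σp³, five levels | 1 − Σp³, eight levels | Ratio |
|---|---|---|---|
| 25% | 0.939 | 0.964 | 1.03 |
| 50% | 0.860 | 0.962 | 1.12 |
| 70% | 0.653 | 0.908 | 1.39 |

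For the last row, the five-level sum of cubes is .000125 + .000001 + .000729 + .003375 + .343 = .347, so the index is 0.653.

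**Where the gain comes from.** Splitting a category of size a + b into a and b raises the index by 3ab(a + b), which is never negative. At 70% good recovery, the single cut of the top category adds 3 × .30 × .40 × .70 = 0.252 of the total gain of 0.255. At 25% it adds 3 × .12 × .13 × .25 = 0.012 of 0.025. The large figure therefore rests almost wholly on one extra cut.

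**Second set of assumptions.** Let T be the share in good recovery. Split the rest 35% dead, 3% vegetative, 30% severe and 32% moderate, and halve the severe, moderate and good-recovery groups. Power is simulated for Spearman's test with 100 patients, log-odds 0.5 per SD of biomarker and 3000 runs.

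| T | Efficiency of five levels relative to eight | 100 patients count as | Power, five vs eight levels |
|---|---|---|---|
| 30% | 0.96 | 96 | 75% vs 76% |
| 50% | 0.90 | 90 | 72% vs 76% |
| 70% | 0.72 | 72 | 57% vs 73% |
| 80% | 0.56 | 56 | 47% vs 71% |

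Splitting the top category 30/70 instead of evenly gives 0.91 at T = 50% and 0.75 at T = 70%. At T = 40% with an even split the efficiency is 0.94. Both sets of assumptions agree: the loss is small up to about 40%, moderate at 50% and substantial from 70%.

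**The case against.** A reader might infer that most patients will sit in the top category. The protocol does not support that. No severity mix is given, and much of the text points to a sicker cohort. Ethical Considerations expects patients often to lack capacity and places the first research scan after ITU discharge. Methodology records ventilation days, ICU days and intracranial pressure. Micro-dialysis is described as routine, and the site is a major trauma and tertiary neurosurgical centre. Outcome Measures closes with "Developing a better understanding of the relationships surrounding severe brain trauma and biomarkers in development". A broader population need not be a mild one, and in a severe or mixed cohort the gain is about 3% to 12%. This stands, and it is why the point is a risk and not a forecast.

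A reader might also infer that differences among well-recovered patients are lost to the study. They are not. The secondary battery can separate some of them, and Statistical Analysis lists cognitive and psychological scoring among its primary dependent variables. The loss is in the Glasgow score alone.

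Three further limits stand. The ordinal analysis is called exploratory and is not tied to the Glasgow score, and the sample size rests on biomarker positivity, so no stated power is undermined. The 39% assumes one common odds ratio, so that the biomarker separates upper from lower good recovery as strongly as death from survival, with no extra misclassification. And the extended scale only divides the top category in two, so it still has a ceiling.

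Finally, because Table 3 omits the Glasgow score, the protocol does not show how or by whom it is obtained, so the added effort cannot be read directly from the text.

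**Conclusion.** The point holds as a risk to the primary outcome. The protocol fixes the unextended score, admits any adult head injury, and leaves its ISS criterion without a value. ISS also grades injury overall, so even a completed value would not by itself set a head-injury floor.

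The gain in information from the extended scale is about 3%, 12% and 39% at 25%, 50% and 70% good recovery. These figures rest on assumed distributions, the standard level structure of both scales and proportional odds. The 39% is not an expected value, since the documents do not show that the cohort will be mostly mild.

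The recommendation does not depend on settling the case mix. The extended scale has at least as high an information index under any distribution, and it collapses to the planned score. This is a worthwhile improvement, not a flaw that invalidates the study.

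**What to change.** - In Outcome Measures, name the eight-level Glasgow Outcome Scale-Extended, by structured interview, as the 6-month primary outcome and the 12-month secondary outcome, analysed as an ordinal scale. Report the collapsed five-level score as a supporting result.
- Add the functional outcome to Table 3 at days 180 and 360, and say who administers it.
- Complete the ISS entry criterion in Methodology and reconcile it with the inclusion criteria in Study Design, so that the severity range of the cohort is known.

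The cost is a protocol amendment and a slightly longer interview. Follow-up contacts at days 180 and 360 are already scheduled, and Ethical Considerations already has a trained psychologist administering tests at follow-up, so no extra visit or assessor should be needed. Comparability with work on the five-level score is kept.
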